|                                                             | A                                                                                                                                       | B1                                                                                                                                                                                                           | B2                                                                                                                                               | C                                                                                                        | D                                                                                                                           |
| Patients with findings compatible with acute Chagas disease | Patients at risk for developing CHF. They have positive serology, neither structural cardiopathy nor CHF symptoms. No digestive changes | Patients with structural cardiopathy, evidenced by electrocardiographic or echocardiographic changes, but with normal global ventricular function and neither current nor previous signs and symptoms of CHF | Patients with structural cardiopathy characterized by global ventricular dysfunction, and neither current nor previous signs and symptoms of CHF | Patients with ventricular dysfunction and current or previous symptoms of CHF (NYHA FC I, II, III or IV) | Patients with refractory symptoms of CHF at rest, despite optimized clinical treatment, requiring specialized interventions |

Arq Bras Cardiol 2011; 97(2 supl.3): 1-48

The **secondary outcome** is determined by the change in plasma levels of biomarkers versus changes in parasite load.

Additional measures of scientific value: (a) change in plasma levels of biomarkers of inflammation and endothelial activation; (b) incidence and severity of AEs; (c) change in parasite burden and serologic response over the follow-up period, measured by quantitative PCR (qPCR); (d) changes in biomarker levels at different follow-up time points and correlation with parasite burden and ATO regimen; and (e) incidence of treatment discontinuation due to severe AEs.

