Finally, a baseline resting ECG and a 2D echocardiogram will be performed. Both tests will be performed at each center. The ECG should be normal or with nonspecific changes (incomplete right bundle branch block, incomplete left anterior fascicular block, mild bradycardia, minor PR interval widening, and minor ST-T changes). Any clinically significant abnormality found on the electrocardiogram will automatically lead to the exclusion of the patient from this study (see exclusion criteria).

After randomization and before starting treatments, patients will undergo a new focused physical examination, and blood will be drawn for qPCR and biomarker determination.

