## 10. SELECTION AND WITHDRAWAL OF SUBJECTS

### 10.1. Inclusion criteria:

Subjects eligible to be enrolled in this trial must be adults older than 18 years and younger than 50 years, weighing more than 40 kg, with a conventional confirmatory serology for *T. cruzi* infection from the Instituto de Salud Pública de Chile (ISPCH). A positive qPCR will be selected to participate in this trial. Only patients with a new diagnosis of Chagas disease in the chronic indeterminate phase will be included. In addition, they must have normal values in laboratory tests for the following parameters: total white blood cell count, platelet count, creatine kinase (CK), alanine aminotransferase (ALT), aspartate aminotransferase (AST), total bilirubin or creatinine, or a gamma-glutamyl transferase (GGT)  $\leq 2$  times the upper limit of normal (X ULN); Women of reproductive age must have a negative serum pregnancy test, must not be breastfeeding, and must consistently use a highly effective method of contraception throughout the treatment phase.

Subjects must also meet all the following criteria: the ability to comply with all tests and follow-up visits specified in the protocol and have a permanent address; sign the written informed consent form.

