### **12.Data analysis and statistical methods:**

#### **12.1. Sample size:**

A sample size of 75 patients per group is sufficient to achieve a power of 90% at an overall significance level of 5% (2-sided), assuming that the proportion of patients who improve electrocardiographic and echocardiographic parameters, as well as the levels of the cardiac function markers BNP and cTnT in the EOT in the experimental treatment group is 0.40. The proportion in the placebo group is 0.20, with an odds ratio of 2.5. Considering an estimated dropout rate of 25%, 100 patients per group (300 patients in total) would be recruited (Fleiss et al., 2003). The study will be sufficiently powered to provide evidence of the superior efficacy of either statin dose plus antichagasic therapy relative to antichagasic treatment alone.

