### **12.4. Efficacy analysis:**

For analysis of the primary outcome, a one-sided Fisher's exact test of the proportion of patients with a significant decrease in biomarker levels in the ITT (primary analysis) and per protocol (secondary analysis) populations will be used. ANOVA test will be performed to analyze differences in variances between the different markers. An exact test will be performed for all secondary comparisons of proportions between ATO versus placebo, including parasitological response to treatment. Latent class and multivariate analyses will assess the association between parasitological response, biomarker changes, and ATO doses.

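### Section 12.1 sizes the trial on an undefined improvement responder that patients admitted without structural heart disease have little room to meet, and 75 per group does not give 90% power even at the assumed rates

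*Protocol*

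**What the plan says.** Section 12.1 states: "A sample size of 75 patients per group is sufficient to achieve a power of 90" per cent, at an "overall significance level of 5% (2-sided"). Success is the "proportion of patients who improve electrocardiographic and echocardiographic parameters, as well as the levels of the cardiac function markers BNP and cTnT", and the assumed rate "in the EOT in the experimental treatment group is 0.40", against 0.20 on placebo, with an odds ratio given as 2.5. Allowing for 25% dropout leads to 100 per group, 300 in all. The section says the trial is powered for either statin dose against antichagasic treatment alone.

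Entry is set elsewhere:

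- Section 10.1: "Only patients with a new diagnosis of Chagas disease in the chronic indeterminate phase will be included".
- Chart 1 (section 9.1) describes this form, stage A, as having "neither structural cardiopathy nor CHF symptoms".
- Section 9.7: "The ECG should be normal or with nonspecific changes", and any clinically significant ECG abnormality excludes the patient.

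Two other sections describe the primary endpoint differently. Section 9.1 uses non-progression or reversion of cardiomyopathy stage relative to phase A at 12 months. Section 12.4 begins "For analysis of the primary outcome, a one-sided" Fisher's exact test and applies it to the proportion with a significant fall in biomarker levels.

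**The concern.** A responder defined by improvement suits patients who start with something abnormal. This trial selects patients who mostly do not. If improvement means correcting an abnormality, someone with a normal ECG and a normal ejection fraction cannot meet the ECG and echocardiographic parts whatever the treatment does, and adds a non-event to every arm. If improvement means any favourable shift, normal fluctuation can count as success and the responder becomes partly noise. The protocol chooses neither meaning, yet applies 0.40 and 0.20 to everyone.

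At stake is the justification for 300 patients. The assumed rates, the responder and the power figure form one argument, and each part is open to doubt.

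**Working it through.** **1. The plan's own figure.** Inputs from 12.1: p1 = 0.40, p2 = 0.20, two-sided 5%, 90% power; equal allocation from the Summary. The usual formula for two proportions (the book by Fleiss and co-authors is cited in 12.1) is

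n = [z(α/2)·√(2·p̄·(1−p̄)) + z(β)·√(p1(1−p1) + p2(1−p2))]² / (p1−p2)², with p̄ = 0.30.

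n = [1.960·√0.42 + 1.282·√0.40]² / 0.04 = [1.270 + 0.811]² / 0.04 = 108.2, so **109 per group**.

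Continuity correction: (108.2/4)·[1 + √(1 + 4/(108.2·0.20))]² = 118.02, so **119 per group**.

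After 25% dropout: 109/0.75 → 146 and 119/0.75 → 159 per group. The plan's own dropout step is right (75/0.75 = 100); its starting figure of 75 is not reproduced.

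**2. Power at 75 per group.** z = [0.20·√75 − 1.270]/√0.40 = (1.732 − 1.270)/0.632 = 0.730, so power is **76.7%**. Exact enumeration of Fisher's two-sided test gives **71.4%**.

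Variants:

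- One-sided 5%, as in 12.4: 85.4% (Fisher 80.9%).
- All 100 per group contributing an outcome, two-sided: 87.6%.
- Both doses pooled against 75 placebo patients: 87.2% two-sided, 93.0% one-sided.
- The stated odds ratio of 2.5 (p1 = 0.385; 0.40 against 0.20 is actually 2.67): 70.4% two-sided at 75 per group.

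No two-sided comparison of a single dose with placebo on these inputs reaches 90%.

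**3. Effect of patients who cannot respond.** Let f be the share with no room to respond. The protocol does not give f, so a range is shown. Assume 0.40 and 0.20 hold only among the other patients; the overall rates are then (1−f)·0.40 and (1−f)·0.20. Power is at 75 per group, two-sided 5%.

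| f (assumed) | Overall rates | Power, normal approx. | Power, Fisher | n per group for 90% |
|---|---|---|---|---|
| 0 | 0.40 vs 0.20 | 76.7% | 71.4% | 109 |
| 0.25 | 0.30 vs 0.15 | 59.6% | 52.7% | 161 |
| 0.50 | 0.20 vs 0.10 | 40.2% | 32.3% | 266 |
| 0.75 | 0.10 vs 0.05 | 21.2% | 12.8% | 582 |

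Alternatively, hold the overall rate at 0.40. Success among patients able to respond must then be 0.40/(1−f): 53% at f = 0.25, 80% at f = 0.50, 100% at f = 0.60. Only beyond f = 0.60 is 0.40 impossible.

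**4. If all four components must improve.** Treating them as independent (an assumption, for illustration), each would need a rate of 0.40^(1/4) = 0.80 on atorvastatin and 0.20^(1/4) = 0.67 on placebo.

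**5. Timing.** Section 12.1 scores the response at EOT, which section 9.5 uses for end of treatment. The schedule in 9.6 places the 2D echocardiogram only at screening and day 360. The protocol gives both two months (Summary, 9.5) and four months (9.3) for atorvastatin. With two months of antichagasic treatment and a two-week gap, treatment would end near day 134 (60 + 14 + 60) or day 194 (60 + 14 + 120), later if liver enzymes delay the start. No echocardiogram is scheduled near either day, so an echocardiographic response at EOT cannot be scored.

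**The case against.** A reader might infer that the 0.40 and 0.20 rates are unattainable and that patients with normal findings fail by construction. The documents do not support that:

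- Improvement is undefined. Sections 8.1 and 8.2 name heart rate, QT duration, QRS duration and morphology, and ejection fraction. Apart from QRS morphology these are continuous and can move within the normal range.
- Section 9.7 admits minor ECG findings, such as incomplete right bundle branch block or mild bradycardia. Section 10.2 names only cardiac stage II or higher as excluded. Section 7.1.1 allows some cardiac involvement in the indeterminate phase.
- No entry criterion limits BNP or cTnT.
- Requiring all components is the natural reading of 12.1, but the section could also be listing the domains assessed.
- The 0.40 and 0.20 are stated for whole groups, so they may already include patients who cannot respond.

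These points stand. They reduce the claim from impossibility to limited room and an unsupported assumption.

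Nor should the whole gap from 90% be put down to limited room. About 13 points (90 − 76.7) exist before any dilution; at f = 0.25 the dilution adds about 17 (76.7 − 59.6). A reader might also infer that a null result would merely reflect the ceiling. That does not follow, because 12.4 does not test the 12.1 composite.

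The objection does not supply a definition or a source for the rates, and it leaves the power error untouched. A later analysis plan could define the responder, but could not make the 90% stated in 12.1 correct.

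**Conclusion.** The point holds in this form. The 12.1 responder is undefined for a population selected to have little to improve, its rates are unsourced and doubtful there, it matches neither 9.1 nor 12.4, and its echocardiographic part cannot be scored at EOT.

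The power error needs no assumption beyond the plan's own inputs: 76.7% (Fisher 71.4%) instead of 90%, or 75 per group where 109 to 119 are needed. The further fall to about 60%, 40% or 21% is conditional on the assumed f and on the rates holding only among patients able to respond. It shows how sensitive the plan is; it does not estimate what will happen.

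**What to change.** 1. In 12.1, withdraw the 90% claim and restate the power at the planned 300 patients. If the present rates were kept, the two-sided figure for one dose against placebo is 76.7% with 75 evaluable per group.
2. Replace the improvement responder with an endpoint that patients starting in stage A can show. State it identically in 9.1, 12.1 and 12.4, with one timepoint, and give the source of the assumed rates or variability.
3. Analyse day-360 ejection fraction and log BNP, and log cTnT where measurable, as continuous outcomes adjusted for the pre-treatment value. Restate 12.1 for the quantity chosen. The protocol gives no standard deviations, so that power cannot be computed here.

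A responder analysis restricted to patients abnormal on every component is not a useful fallback, since entry would leave few of them.

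Cost: revision of 9.1, 12.1 and 12.4, and no new measurements, because echocardiography at screening and day 360 and biomarkers at day 0 and day 360 are already scheduled. The stated power will be less favourable, and the responder proportion will no longer be the sizing quantity. Continuous outcomes let every measured patient contribute, but a healthy ejection fraction or very low cTnT still limits how large an effect can be seen.

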#### **12.2. Randomization and treatment allocation:**

A computer-generated randomization list will be prepared and stratified by center using a block size of twelve. Each center will receive a list of randomization numbers and corresponding ATO or placebo packages. After patient enrollment, the following randomization number available at the

center will be assigned (in chronological order), and the corresponding treatment package will be delivered.

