## 9.3. Study description:

This is a proof-of-concept Phase II clinical trial with three different groups: Two groups will receive antichagasic therapy plus 40 or 80 mg/day of ATO. The third group will receive a placebo plus antichagasic therapy. The placebo is justified as long as the patient receives the complete conventional antichagasic treatment; therefore, the management of his Chagas disease is assured. In this clinical trial, the placebo will be a nutritional supplement tablet with an appearance similar to that of ATO. This product was chosen given the potential difficulties in manufacturing a small number of pills since the trial does not have a pharmaceutical industry sponsor capable of manufacturing it under Good Manufacturing Practice standards.

Nutritional supplements do not affect vascular or cardiac inflammatory parameters and therefore do not introduce confounding elements in the comparative analysis with atorvastatin.

Patients will first receive conventional antichagasic therapy for two months. After two weeks (or until normalization of liver enzymes), treatment with atorvastatin or placebo will be initiated for

four months. These doses were chosen to minimize false negative results, thus providing the best hypothesis test and maximizing the pharmacodynamic effect on inflammation and cardiac and endothelial function. In addition, the treatment sequence aims to minimize adverse reactions that could be caused by the eventual combination of antichagasic drugs with atorvastatin. Study subjects will be randomized, and the three groups will be double-blinded (both clinical investigators and subjects will be blinded) to ATO or placebo. However, antichagasic therapy will be open-labeled. In addition, qPCR and the other laboratory evaluations, as well as ECGs and 2D echocardiograms, will be performed with the clinical investigators blinded to ATO or placebo allocation.

This study will be conducted in four centers: 1) Hospital San Juan de Dios and 2) Hospital Felix Bulnes in Santiago, Metropolitan Region, 3) Hospital [name] in Viña del Mar, 4) Hospital San Martin de Quillota, Valparaiso Region. Each center annually admits 60 new patients to its Chagas Control Program (CCP). These four centers are part of the care network of the National Chagas Disease Control Program.

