### 10.2. Exclusion criteria:

Signs and symptoms of the digestive form of CD; stage II or higher chronic cardiac CD; acute or chronic health conditions such as acute infections, history of HIV infection, diabetes, liver and kidney disease; pre-existing heart disease unrelated to Chagas disease; hypothyroidism, and family history of muscle disorders; formal contraindication to receiving NFX or BZD, known history of hypersensitivity, allergy or severe adverse reactions to ATO, BZD or NFX; history of prior treatment

for CD; history of previous treatment with atorvastatin, lovastatin, rosuvastatin, simvastatin or any other statin; any concomitant use of antimicrobial agents; history of alcohol or drug abuse; any condition that precludes oral medication; concomitant or intended use of CYP3A4 modifiers; a medical history of familial short QT syndrome or concomitant therapy with drugs that may shorten the QT interval. Abnormal laboratory test values for the following parameters: total white blood cell count, platelet count, creatine kinase (CK), alanine aminotransferase (ALT), aspartate aminotransferase (AST), total bilirubin or creatinine, or a gamma-glutamyl transferase (GGT) > 2 times the upper limit of normal (X ULN); Pregnant or lactating women; refusal to use a highly effective method of contraception during the treatment phase.

Patients meeting the selection criteria will undergo the randomization procedure. Only subjects enrolled in this trial will receive the study drugs. Patients will be assigned, in ascending order, a trial identification number (TIN) according to the enrollment order. A patient is considered randomized when s/he receives a TIN.

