## **11. Subject treatments**

### **11.1.1. Doses and treatments regimens**

Tablets of 40 and 80 mg of ATO will be purchased from a pharmaceutical laboratory with current sanitary registration recognized by the ISPCH, offering the active ingredient in a bioequivalent formulation. The placebo tablets will correspond to a nutritional supplement tablet supplied by a registered provider.

The purchase will be made through the Pharmacy of the Clinical Hospital of the University of Chile.

The ATO and placebo tablets will be repackaged in black plastic bottles of 200 ml capacity, previously sterilized with UV light, under aseptic conditions using a type II biosafety hood. The bottles will contain 120 tablets each and all from the same lot to allow the traceability of the drug.

The labeling of each bottle will be done as required by good manufacturing practices, including a) name and contact information (telephone and e-mail) of the principal investigator; b) dosage form, route of administration, number of units; c) lot number and code (assigned by the principal investigator) of the supplier laboratory; d) project code; e) instructions for use; g) randomization code; f) warning: "for clinical trial use only"; h) expiration date; i) the phrase: "Keep out of the reach of children."

The antichagasic drugs NFX or BZD will be supplied by the Chilean Ministry of Health as part of the PCC. The antichagasic treatment will be administered according to the indications of the "Manual de Procedimientos para la Atención de Pacientes con Chagas" (MINSAL, 2017), and the administration of ATO, antichagasic drugs, and placebo treatment will be monitored at each of the patients' visits to determine tablet accounting and compliance with the drugs. BZD dosing will be 5 mg/kg/day every 12 hours (BID), and NFX dosing will be 5-10 mg/kg/day BID. ATO doses will be 40 and 80 mg/day for each group and will be administered in the morning.

At each visit, the patient will be required to bring all remaining study medications at the 30th, 60th, 120th, and 180th-day visits to check compliance with the prescribed antichagasic and experimental treatment and perform medication accounting (Torrico et al., 2018). **If a subject develops**

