### **12.6. Criteria for early termination of the study**

The principal investigator reserves the right to terminate the study at any time before including the planned number of subjects for valid scientific or administrative reasons. Reasons for study termination may include, but are not limited to, the following:

- Extremely low enrollment rate or lack of eligible patients
- High frequency of protocol violations
- Inaccurate or incomplete data
- Unsafe or unethical practices
- Following the recommendation of clinical ethics committees

If the study is terminated early, the clinical investigator is required to

- Complete all CRFs to the fullest extent possible and return all implements, CRFs, and related study materials provided to him/her.
- Respond to all principal investigator questions related to enrolled subjects' data at the site before study termination.
- Ensure that subjects enrolled in the study who have not yet reached a follow-up point receive necessary medical care.

- The investigator should provide written reasons for his or her decision to the national health authority and the sponsor

The investigator should provide written reasons for his or her decision to the national health authority and the ethics committee.

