### **16.1. Case Registration Forms (CRF)**

The data of each study participant will be collected by the responsible clinical researcher (RCI). Study-specific information will be entered into an electronic CRF (CRF), hosted on the RedCap platform of the Faculty of Medicine of the University of Chile, an encrypted electronic platform designed to safeguard clinical and biomedical research data.

All data entered into the CRF will be anonymous and identified exclusively by the unique patient number (NUP), assigned consecutively for each center as participants are recruited and is independent of the randomization code of the assigned treatment. This NUP is provided by the Principal Investigator (PI) of the study at the request of the ICR at each center at the time of recruiting the participant and after signing the Informed Consent Form. On the RedCap platform, the NUP will be replaced by a randomly generated code, breaking the link between the NUP and the platform. Similarly, the center and the clinical investigator will receive a unique, electronically generated code so that the patient's unique code will not be associated with the name of the clinical investigator or the study center.

The project's principal investigator will not collect personal information from study subjects in the CRF. Personal information is understood to be the name (including initials), residence address, and the commune in which the subject lives. Only the Region of origin will be recorded, nor will the contact telephone number, the exact date of birth, or any other information that would lead to the identification of the subject being recorded. Data such as family income, occupation, or educational level will not be registered, as they are not variables relevant to this study. However, the clinical investigator should maintain contact information for each participant so that all participants can be quickly contacted by the clinical investigator, if necessary.

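### Allocation concealment and blinding are not secured: bottles carry lot and supplier marks coded by the principal investigator, who is not named as blinded, and the one block size is published

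*Protocol*

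**What the plan says.** **Allocation (Protocol 12.2).** "A computer-generated randomization list will be prepared and stratified by center using a block size of twelve". Then: "Each center will receive a list of randomization numbers and corresponding ATO or placebo packages". Numbers are used in chronological order after enrolment. The section does not name who generates or holds the list, and does not say whether the centre's copy shows the arm.

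**Packaging and labels (11.1.1).** ATO and placebo tablets are repacked in black bottles of 120, all from one lot. The label carries a randomisation code and also "lot number and code (assigned by the principal investigator) of the supplier laboratory". ATO is bought from a pharmaceutical laboratory, and the supplement comes from a registered provider. Section 9.3 says the supplement tablet looks similar to ATO.

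**Who is blinded (Summary and 9.3).** "the three groups will be double-blinded (both clinical investigators and subjects will be blinded) to ATO or placebo". The principal investigator is not mentioned.

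**What the principal investigator does.** This role approves changes to the prohibited-drug waiting periods (footnote to the Summary table), receives every SAE report within 24 hours (11.2.2), and under 12.6: "The principal investigator reserves the right to terminate the study at any time before including the planned number of subjects".

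**The concern.** The black bottle and the similar tablet hide the contents, but a lot number or supplier code printed on the outside can undo that. A lot belongs to one product. If the three products carry different marks, bottles fall into visible groups, including those still on the centre's shelf. Once one bottle of a group is identified, the rest of the group is too. A person enrolling the next patient could then recognise the arm. The clinical investigators, who also judge AE causality and decide on stopping treatment (11.2.4), could recognise it for patients already treated.

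The second weakness is the principal investigator's position. Whoever assigns the supplier code knows which code means which product. That knowledge sits with the role that handles waiting-period changes, SAE reports and termination, and no text places the role inside the blind.

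Selective enrolment destroys baseline comparability, and an ITT analysis cannot restore it. Knowledge of treatment when AEs or termination are being considered is equally beyond repair at the analysis stage.

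**Working it through.** The protocol gives no figure for predictability, so there is none to reproduce. The main question is settled by reading, and the sizes below are conditional.

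**1. Are the marks arm-specific?** 11.1.1 puts lot number and supplier code on every bottle. There are three products: ATO 40 mg, ATO 80 mg and the supplement. Three products cannot share one lot, so lot numbers should differ by arm. Whether the suppliers also differ is likely from the two descriptions but is not stated.

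**2. How far could one unblinding reach?** Assume one lot per product, one bottle per patient and four equal centres. Bottles per arm per centre = 100/4 = 25. One identified bottle leaves 25 − 1 = 24 others at that centre with the same mark. With several lots per product the number is smaller, but no lot would span two arms.

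**3. Could a mark be decoded without formal unblinding?** The scheduled panel includes LDL cholesterol at day 120 and later, it is run in each centre's own laboratory (9.7), and 7.2 says ATO is used to lower LDL. Nothing withholds these results. This is a possible route, not a stated one.

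**4. Fixed block of twelve: upper bound if all earlier arms in the block are known.** The allocation is 1:1:1, so each block is 4:4:4.
- An assignment is certain when all remaining places belong to one arm. The probability that the last k places are all one arm is 1 for k = 1; 3/11 for k = 2; (3·2)/(11·10) = 6/110 for k = 3; (3·2·1)/(11·10·9) = 6/990 for k = 4.
- Expected certain assignments = 1 + 0.2727 + 0.0545 + 0.0061 = 1.33 per block; 1.33/12 = 11.1%.
- Best guess (the arm with most places left), by exact recursion G(a,b,c) = max(a,b,c)/n + Σ (x/n)·G(one fewer of x), with n = a + b + c: G(4,4,4) = 6.144; 6.144/12 = 51.2%, against 33.3% by chance.
- For ATO (either dose) against placebo, 8:4: 2.04 of 12 are certain (17.0%), and the best guess is right 71.7% of the time, against 66.7% by always naming ATO.

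**5. Is that bound likely to be reached?** Take equal centres and the planned 24 months (about 730 days). Each centre enrols 300/4 = 75 patients, one every 730/75 = 9.7 days. The twelfth patient of a block enters 11 × 9.7 = 107 days after the first. ATO or placebo starts at about day 60 + 14 = 74, and the next scheduled laboratory visit is day 120. The block is therefore normally full before even its first patient has a scheduled on-treatment result. The margin is thin: at 120/11 = 10.9 days per patient (730/10.9 ≈ 67 patients at a centre) the first result would arrive in time. But that reveals one arm at most, not all eleven. The 51% and 11% are ceilings, not expectations.

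**The case against.** The strongest reply is that the protocol already describes masking, and that the worst readings go beyond the text. Much of this stands.

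- **The list.** A reader might infer that centres can see the coming arms. The text says a list of numbers, with packages to match. A list showing arms would contradict the stated blinding of the clinical investigators who enrol. Coded numbers with masked packages is at least as natural a reading, so full knowledge of future assignments should not be alleged.
- **The recruit's number.** A reader might also infer that the principal investigator controls allocation because of 16.1: "This NUP is provided by the Principal Investigator (PI) of the study at the request of the ICR at each center". The same section makes that number independent of the randomisation code, and it is issued after consent. It allocates nothing.
- **The principal investigator.** Nothing says this role holds the randomisation list. That the role is unblinded is inferred from its omission and from its task of assigning the code. 11.2.6 leaves opening the blind to the treating physician rather than the investigator responsible for the project, which suggests the intention was to keep that role blind.
- **The block size.** Twelve is four times the minimum for three arms, and predictability arises only if blinding has already failed.

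Two things remain. Black bottles and similar tablets do not neutralise a lot number and supplier code on the label. And if 11.2.6 means the project lead to stay blind, 11.1.1 works against it by giving that person the product code. These are arrangements the protocol states, not details left to an analysis plan.

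**Conclusion.** The point holds as a weakness in the stated arrangements. The protocol neither discloses upcoming allocations nor secures that they stay hidden. Three features should change: label marks that may identify the arm, a product code assigned by a role not named as blinded, and one published block size.

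The conclusion rests on an inference, that the three products carry different lots. The reach of 24 further bottles per centre also needs one lot per product, one bottle per patient and equal centres. The block figures (51% and 11%) apply only if every earlier arm in the block is known, which the enrolment pace and visit schedule make unlikely. No bias is shown to have occurred. If masked labels and independent list custody already exist in practice, what remains is mostly wording. The change is worth making because the harm, if it occurred, could not be corrected later.

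**What to change.** - **11.1.1:** Give the product code key to someone with no role in enrolment, AE handling or data, for example the hospital pharmacy that already buys the product. Put kit numbers on the bottles in place of arm-identifying lot or supplier marks, and let the key holder keep the link to lot and supplier for traceability.
- **9.3 and Summary:** Add the principal investigator to those blinded.
- **12.2:** State that the centre's list carries kit numbers only, and who generates and holds the full list. Use randomly varied block sizes (for example 6, 9 and 12) that are not disclosed to sites.

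**Cost:** a new computer-generated list and revised wording. The pharmacy currently has only a purchasing role, so it would take on custody of the key and must be reachable for the emergency procedure in 11.2.6. The protocol ties its label contents to good manufacturing practice, so the revised label should be checked against that. A possible imbalance of a few patients per centre remains. With twelve as the largest block, an unfinished block can leave two arms at most 4 − 0 = 4 apart at a centre, the same bound as now.
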